### Statistical analysis

The prevalence of polyps in each group, the primary endpoint, will be compared between the metformin group and placebo group by the chi-square test. The safety, one of the secondary endpoints, will be similarly compared by the chi-square test. The remaining results in the two groups will be compared by the Mann-Whitney *U *test or Student's *t *test. A P value of < 0.05 shall be regarded as indicative of significance. The analysis will be performed using SPSS, version 17.0 (SPSS Inc., Chicago, Il.).

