### Outcome measurements

The primary endpoint shall be the prevalence of colorectal polyps and number of polyps after 1-year's intervention. The endoscopic examinations and polypectomies will be performed using Olympus colonoscopes (model H260AZI). The day before the endoscopy, each patient will be instructed to consume a low-residue diet and shall receive 5 mg of oral sodium picosulfate. On the day of the endoscopy, the patients shall receive 2000 ml of polyethylene glycol (PEG). If the feces are not sufficiently clear, an additional 1000 - 2000 ml of PEG may be given to ensure sufficient bowel cleaning. At the time of the polypectomies, the endoscope shall be inserted into the cecum, and the entire colorectum will be carefully observed as the endoscope is pulled back. If any polyps are detected, polypectomy will be performed. At the end of 1 year of administration of metformin/placebo, the same endoscopists will perform the repeat endoscopic examinations. If a polyp(s) is detected at the repeat colonoscopy (after treatment for one year), a biopsy will be performed. A total of 6 endoscopists from Yokohama City University Hospital and the 5 affiliate hospitals will perform the polypectomies and endoscopic examinations. All procedures will be recorded on DVD, and all the polyps will be photographed. The number of polyps in each patient will first be counted by the operators during the performance of the colonoscopy. To further ensure validity, the number of polyps will be counted again through observation of the recorded DVD by 3 blinded expert endoscopists ([name], [name], and [name]). If these expert endoscopists judge the colonoscopic examination as having been inadequate in any case, that case will be excluded. The biopsied polyps will be evaluated by expert pathologists ([name] and [name]).

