### Randomization

The investigator shall convey the patient's details to the central registration centre via fax. After an eligibility check, the patients will be randomly assigned to receive metformin or placebo at the central registration centre by a computer program, using a minimization method, with stratification by institute, age, gender and BMI. In this way, the patient assignment will be concealed from the investigator. The randomization center will allocate a numbered treatment pack to each patient, which will contain all the drugs or placebos needed to complete a course of the trial treatment for one patient.

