### Sample size estimation

We previously showed that metformin administered at 250 mg/d for 1 month directly suppressed the formation of ACF. In that study, mean number of ACF per patient decreased significantly from 8.78 ± 6.45 (baseline) to 5.11 ± 4.99 (at 1 month, *p = 0.007*) [20]. Based on a similar study, Takayama et al. reported that sulindac administration at 300 mg/d for 2 months to post-polypectomy patients suppressed ACF formation, decreasing the number of ACF from 7.70 ± 4.04 (baseline) to 4.00 ± 2.95 (at 2 months, *p < 0.001*) [26]. From these reports, we estimated that metformin and sulindac may have equivalent effect on suppression of ACF formation. Moreover, from the same study, Takayama et al. reported that in the post-polypectmoy patients who received 2-months' intervention, the number of polyps (hyperplastic polyp and adenoma) at 1 year after the treatment was significantly lower in the sulindac group in comparison with that in the placebo group (26/48 (54.2%) vs. 15/48 (31.3%), *p = 0.025*) [26]. Therefore, we speculated that 1-year's treatment with metformin might yield equivalent suppression of metachronous polyp formation to that with sulindac. To detect the reduction in the number of metachronous polyps in the metformin group using the chi-square test with a two-sided significance level of 5% and a power of 80%, it was found that a sample size of 68 patients per group would be necessary. Assuming a 10% dropout rate, we propose to recruit 75 patients per group, that is, a total of 150 patients.

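### Allocation is minimised on institute, age, gender and BMI, but the primary chi-square test ignores them; if they predict polyps, the test is conservative and forgoes a modest gain in power

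*Protocol article*

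**What the plan says.** Under Randomization, the protocol article assigns patients centrally by computer, "using a minimization method, with stratification by institute, age, gender and BMI". Under Statistical analysis it fixes the primary comparison: "The prevalence of polyps in each group, the primary endpoint, will be compared between the metformin group and placebo group by the chi-square test". Other outcomes also get two-group tests without covariates ("The remaining results in the two groups will be compared by the Mann-Whitney" test or the t test). Sample size estimation uses the same chi-square test and finds that "a sample size of 68 patients per group would be necessary". No section names an adjusted or stratified analysis.

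The article gives some reason to think the balancing factors matter. Eligibility criteria justifies the lower age limit by the rarity of polyps in the young, and Background links obesity to colorectal cancer. Outcome measurements adds: "A total of 6 endoscopists from Yokohama City University Hospital and the 5 affiliate hospitals will perform the polypectomies and endoscopic examinations".

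**The concern.** Minimisation makes the arms more alike on the chosen factors than simple randomisation would. If those factors predict polyps, the difference in prevalence varies less from one possible allocation to another than the chi-square formula assumes. The standard error behind the test is then too large, and its true type I error falls below 5%.

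At stake is sensitivity: a real effect could be missed that an analysis using data already held at registration would have found. The trial has little power to spare, as the first step of the working shows.

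**Working it through.** **Inputs.** From Sample size estimation: 26/48 = 0.5417 and 15/48 = 0.3125, two-sided 5%, 80% power, 68 evaluable per group (136 in all). From Study design and setting: six institutes. Not in the documents, hence assumed and ranged: how strongly the factors predict polyps, and the random element of the minimisation.

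**1. The plan's own figure.** The unpooled normal formula gives (1.960 + 0.842)² × (0.2483 + 0.2148) / 0.2292² = 69.2, so 70 per group. The pooled form usual for a chi-square test gives 72. The stated 68 is close to the first. Power at 68 is 79.3% (unpooled) or 77.7% (pooled).

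**2. Approximation.** Let the balanced factors explain a share R² of the outcome variance. The chi-square standard error is then too large by 1/√(1−R²). The true type I error is 2[1 − Φ(1.960/√(1−R²))]. Adjusted power at 68 is the pooled power at 68/(1−R²). For R² = 0.10, 1.960/√0.90 = 2.066, which gives 0.039.

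| R² (assumed) | Standard error too large by | True type I error | Adjusted power (unadjusted 77.7%) |
|---|---|---|---|
| 0 | 0% | 5.0% | 77.7% |
| 0.05 | 2.6% | 4.4% | 79.8% |
| 0.10 | 5.4% | 3.9% | 81.9% |
| 0.20 | 11.8% | 2.8% | 86.2% |

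**3. Simulation.** There were three separate sets of simulated trials, each with 136 patients, six sites and minimisation. Set A used 2,500 trials per setting and set B 4,000. Sets A and C used a 0.8 biased coin. The adjusted model contains the four factors only.

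| Set and assumed effect | Chi-square type I error | Chi-square power | Adjusted power |
|---|---|---|---|
| A weak | 4.8% | 79.2% | 81.0% |
| A moderate | 4.2% | 79.2% | 82.8% |
| A strong | 3.2% | 79.6% | 84.6% |
| B moderate | 3.7–3.8% | 77.5–78.0% | 80.6–81.2% |
| B strong | 3.0% | 78.0% | 85.3% |
| C none | 5.4% | 78% | 79% |
| C weak | 4.1% | 79% | 81% |
| C moderate | 4.0% | 78% | 82% |
| C strong | 2.7% | 80% | 87% |

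With 4,000 trials the Monte Carlo standard error is √(0.05×0.95/4000) = 0.3 points for type I error and √(0.8×0.2/4000) = 0.6 points for power. In set B the chi-square standard error exceeded the actual spread by about 1–3% with moderate effects (for example 0.0848/0.0830 = 1.02) and by 8–9% with strong effects (0.0819/0.0759 = 1.08; 0.0849/0.0782 = 1.09).

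**4. Comparison at equal size.** In set A the adjusted Wald test ran at 6.0/5.6/5.8%, so part of its gain is excess type I error. Shifting to a true 5% uses Φ(z + Φ⁻¹(power) − 1.960), with z the critical value at the actual size. For the weak setting, 1.881 + 0.878 − 1.960 = 0.799, or 78.8%. The three settings become 78.8/81.5/83.0%, gains of −0.4/2.3/3.4 points. In set B the standardised risk difference held 4.7–5.2% under the null. It gained 2.2–2.8 points with moderate effects (for example 80.6 − 77.8) and 6.9 with strong effects (84.9 − 78.0).

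**5. Baseline polyp number.** In set B, adding it at an assumed log-odds of 0.3 or 0.6 per polyp took power to 82.0% or 85.0% with moderate factor effects. At 0.6 with strong factor effects it reached 88.8%.

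**6. Model size.** Intercept, arm, five institute terms, age, gender and BMI make 10 parameters. Expected events are 68×0.5417 + 68×0.3125 = 36.8 + 21.3 = 58.1, or about 5.8 per parameter.

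**The case against.** The chi-square test is valid here, and the sample size was computed for it, so design and analysis agree. That stands, and it rules out several stronger readings that a reader might infer.

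- *That the trial loses planned power.* It does not. Chi-square power stayed at about 78–80% in every setting. The shortfall is only against a different analysis.
- *That a positive result would be unsafe.* With prognostic factors the error is conservative, so a significant result stands. No confidence interval is planned in the article either, so the excess width concerns the standard error inside the test.
- *That leaving out the baseline polyp number is an error.* It is not a minimisation factor, so omitting it does not distort the test. The article calls post-polypectomy patients high-risk but says nothing of the number removed. Chance imbalance in it is already covered by the 5% error rate.
- *That institute stands for endoscopist.* Six endoscopists over six hospitals makes this plausible, but the article does not say there is one at each.

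The article's hints about age and BMI are indirect. The young are excluded by the 40-year limit, and obesity is linked to cancer, not to polyp recurrence. Plain logistic regression would also exchange a conservative test for a slightly liberal one.

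It could be said that adjustment belongs in an analysis plan that is not shown. Supporting analyses may well be there, but the article itself names the primary test, and that choice is what is questioned.

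**Conclusion.** The mismatch between allocation and primary test is certain from the text; its size is not. Over assumed weak to strong effects, the chi-square runs at about 2.7–4.8% and gives up roughly 2–7 points of power against adjustment for the four factors. Correcting for unequal test size brings the gain to about 2–3 points with moderate effects and nothing visible with weak ones. If the factors are not prognostic, nothing material is lost: set C gave 78% against 79%, and a run in the set B design with 1,500 trials gave 78.5% against 79.8%. This is an inefficient choice that is cheap to improve. It does not threaten the validity of the trial.

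**What to change.** Before unblinding, pre-specify as primary an analysis of any polyp by arm, adjusted for institute, age, gender and BMI. Logistic regression with a Firth or re-randomisation P value is one suitable form. Report the adjusted odds ratio and the standardised risk difference, each with a 95% confidence interval, and keep the unadjusted chi-square as a supporting analysis. Baseline polyp number may be added as one further pre-specified covariate, for precision only.

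The small-sample P value is part of the recommendation: with about 10 parameters for about 58 events, plain logistic tests ran at about 5–6.5%. The simulations above did not evaluate the Firth or re-randomisation versions, so the chosen one should be checked by simulation under the actual minimisation settings before it is fixed. The cost is a paragraph of analysis-plan text and a few lines of code, with no new data and no extra patients.

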The secondary outcomes are (1) the drug safety; adverse events will be monitored by the doctor at every follow-up visit to the outpatient clinic. Adverse events will be graded according to the National Cancer Institute Common Toxicity Criteria for Adverse Events (NCI-CTCAE), version 4.0. Diarrhea, the most frequent adverse event related to use of metformin, will be watched for spontaneous resolution within a few days and/or managed by antiflatulent drugs. If Grade 3 or more severe adverse events appear, the follow-up doctor shall report it (them) to the coordinating office and the case will be withdrawn from the study at that point; (2) laboratory data (fasting blood glucose, fasting blood insulin, HbA1c, total cholesterol, LDL-cholesterol, blood urea nitrogen (BUN), creatinine); (3) the number of ACF. At the time of the 1-year colonoscopy and polypectomy, the lower rectal region from the middle Houston valve to the dentate line will be washed thoroughly with water, sprayed with 0.25% methylene blue, which would be left to stand for 2 min, then again washed thoroughly with water. The number of rectal ACF will be counted with a magnifying endoscope [21]; (4) physical examination findings (body weight, body mass index (BMI)). Metformin is widely used as an antidiabetic drug that improves insulin resistance. The effect of metformin on insulin resistance and the plasma lipid profile will be evaluated by comparing these parameters measured at the baseline and at 1 year in the metformin group and placebo group. All participants will receive physical examination and laboratory tests at the time of the 1-year endoscopic examination and polypectomy; (5) effects of metformin on the cell-proliferative and apoptotic activities in the rectal epithelium and polyps (if any). Colonic epithelial samples will be obtained from the same trial patients by biopsy at the time of the 1-year colonoscopy and polypectomy. The cell-proliferative activity will be evaluated by staining for the proliferative cell nuclear antigen (PCNA), and the cell-apoptotic activity by the terminal deoxynucleotidyl transferase-mediated dUTP-biotin nick end labeling (TUNEL) method; (6) expression levels of protein (AMPK, mTOR/S6K) in the rectal epithelium and polyps (if any) that are thought to be pharmacological targets of metformin. The expression levels of these proteins shall be determined by western blot analysis.

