This trial may have the following limitations. First, we do not propose to conduct a dose-response study of the effect of metformin on colorectal polyp formation. Until now, trails of metformin for cancer prevention and adjuvant treatment have been conducted using high-dose metformin (500 - 2000 mg per day). However, high-dose metformin use is associated with the risk of development of lactic acidosis and gastrointestinal adverse effects (including diarrhea). Gontier et al. reported from a PET/CT study, that subjects treated with antidiabetic agents, including metformin, showed high and diffuse bowel uptake of 18 F-FDG [33]. This suggests that AMPK is present in abundance in the bowel epithelium and that activation of AMPK by metformin up-regulates the expression of glucose transporters. We showed in a previous study that oral low-dose metformin (250 mg per day) suppressed the formation of human colorectal ACF and was also safe, leading us to surmise that oral low-dose metformin may also be effective for CRC chemoprevention. Therefore, we planned to conduct this trial with low-dose metformin. Second, repeat colonoscopy at 1 year may be too short to allow reliable detection of differences between the groups. However, this is first chemoprevention study of metformin for CRC, long-term administration of placebo to post-polypectomy patients may entail ethical problems. Therefore, this time we planned repeat colonoscopy at 1 year. In order to detect the effect of metformin with less effort, we elected to select participants who had undergone polypectomy for this trial, because these patients constitute a high-risk group for the development of metachronous colorectal polyps and/or CRC [5]. And after safety of chronic metformin administration for non-diabetic patients is confirmed, we would like to follow up the participants of this trial, and conduct long-term chemoprevention trial for CRC.

If metformin were found to be effective for the prevention of CRC, the impact would be extremely large. We consider it of interest, therefore, to determine whether metformin might suppress the formation of human colorectal polyps.

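### The only between-group safety analysis stated is a chi-square test at P < 0.05, which cannot supply the confirmed safety on which the later work depends

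*Protocol article*

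**What the plan says.** The abstract and the end of the Background name the safety of metformin in non-diabetic post-polypectomy patients as an aim alongside efficacy. Under Outcome measurements, safety is the first secondary outcome. Adverse events are monitored at follow-up visits and graded by CTCAE version 4.0, and those of Grade 3 or above are reported to the coordinating office. That section also describes diarrhoea: "Diarrhea, the most frequent adverse event related to use of metformin". No expected event rate is given for either arm.

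The Statistical analysis section fixes the comparison: "The safety, one of the secondary endpoints, will be similarly compared by the chi-square test". The threshold is general: "A P value of < 0.05 shall be regarded as indicative of significance". No margin, target difference or interval is given for safety.

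The Sample size estimation section works from polyps alone: "it was found that a sample size of 68 patients per group would be necessary", and then "Assuming a 10% dropout rate, we propose to recruit 75 patients per group, that is, a total of 150 patients".

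The Discussion, in its paragraph on limitations, places follow-up of the participants and a long-term chemoprevention trial "after safety of chronic metformin administration for non-diabetic patients is confirmed". It does not say what would count as confirmation.

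**The concern.** The stated method and the stated use of the result do not fit. A chi-square test asks whether the data show a difference between the arms. The Discussion needs an affirmative conclusion that the drug is safe. If the test is non-significant, the data may still be compatible with a sizeable excess of adverse events, and for uncommon events that is the likely outcome even when the true rate has doubled. No other criterion for the affirmative conclusion is offered.

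The later work would expose non-diabetic people to the drug for longer. A safety statement stronger than the data allow would carry forward into that decision.

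**Working it through.** **Inputs from the article.** Chi-square test and P < 0.05 (Statistical analysis); two-sided 5%, 80% power, polyp rates 26/48 and 15/48, 68 evaluable and 75 recruited per group (Sample size estimation).

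**Inputs assumed.** Placebo event rates of 1% to 20%, and a doubling as the effect. Neither is in the article.

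**1. The article's own sample size.** With unpooled variance, n = (1.960 + 0.842)² × [p1(1 − p1) + p2(1 − p2)] / (p1 − p2)². With p1 = 26/48 and p2 = 15/48, this is 7.849 × (0.2483 + 0.2148) / 0.2292² = 69.2, so 70 per group, within two of the stated 68. The pooled formula gives 72. For dropout, 68 × 1.1 = 74.8, hence 75. The size is therefore roughly reproduced, and it rests on polyps. No power figure is stated for safety.

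**2. Power of the planned safety test.** For each pair of true rates (r on placebo, 2r on metformin), the binomial probabilities of all tables whose Pearson statistic exceeds 3.84 were summed.

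| Assumed placebo rate → doubled rate | 75 per arm | 68 per arm |
|---|---|---|
| 1% → 2% | 3% | 3% |
| 2% → 4% | 9% | 8% |
| 5% → 10% | 22% | 20% |
| 10% → 20% | 41% | 37% |
| 20% → 40% | 77% | 73% |

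For 80% power to detect a doubling, the normal-approximation formula needs 1141 per group from 2%, 435 from 5%, 199 from 10% and 82 from 20%.

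**3. What a non-significant result leaves open.** Take 7 of 75 on metformin and 4 of 75 on placebo, an illustrative result.
- Chi-square: difference 0.0400, pooled rate 11/150 = 0.0733. The statistic is 0.0400² / (0.0733 × 0.9267 × 2/75) = 0.883, so P = 0.35.
- Wilson 95% limits: 9.33% (4.59% to 18.03%) and 5.33% (2.09% to 12.93%).
- Newcombe lower limit: 4.00 − √[(9.33 − 4.59)² + (12.93 − 5.33)²] = 4.00 − 8.95, or −4.9 points (unrounded −4.9499).
- Newcombe upper limit: 4.00 + √[(18.03 − 9.33)² + (5.33 − 2.09)²] = 4.00 + 9.28 = +13.3 points.

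The test reports no significant difference, while an excess of 13 points is not excluded. Two events in each arm give −6.8 to +6.8 points. No events among 75 patients leave an exact upper 95% limit for the rate of 1 − 0.025^(1/75) = 4.8%.

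**4. Precision in general.** With equal rates and 75 per arm, the 95% half-width is 1.96 × √[2p(1 − p)/75]: 5.5 points at 3%, 7.0 at 5% and 9.6 at 10%.

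**The case against.** The strongest reply is that the misuse is not in the text. A reader might infer that P ≥ 0.05 will be taken as proof of safety. The article does not say so. The sentence in the Discussion is a statement of intent, sets no decision criterion and does not mention the chi-square test. This stands, and the point is accordingly limited to a mismatch between the stated method and the stated use.

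A reader might also infer that power is uniformly poor. That depends on event rates the article does not give. From 20% a doubling would be detected with 77% power, so for a frequent event, possibly diarrhoea or any adverse event, the test is far more informative. Nor is low power on a secondary endpoint an error, since it follows from sizing the trial on polyps.

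A third tempting reading is that the chi-square test is all the safety evidence there is. It is not. The article also describes grading, reporting of severe events, visits every four weeks, laboratory measurements and monthly monitoring, and names a data monitoring committee. These collect and manage events, but none supplies a rule for concluding that safety is confirmed.

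A reader might further object to the test itself when counts are small. Exact enumeration puts its size at no more than 5.3% over event rates of 0.2% to 30%, so the choice of test is not the fault.

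Finally, intervals and event tables may be in a full protocol or SAP that is not shown. That is fair for table layout. It does not settle the matter, because the method and the use of the result are both stated in the article.

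**Conclusion.** The point holds in a limited form. The article names a difference test as its one between-group safety analysis and makes later work depend on confirmed safety without a criterion. At 75 per arm, non-significance cannot provide that confirmation for uncommon events: power for a doubling is 3% to 22% for assumed placebo rates of 1% to 5%. It reaches 41% at 10% and 77% at 20%, so the point weakens as events become common. The power figures rest on the assumed rates, the assumed doubling and full retention. With 68 per arm they are slightly lower. The limits in the 7 versus 4 example do not depend on any assumed rate, but the counts are illustrative. This should be corrected. It does not threaten the primary comparison and is no evidence that the drug is unsafe.

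**What to change.** In Statistical analysis, make the primary safety summary the risk difference, metformin minus placebo, with a score-based 95% confidence interval (Newcombe or Miettinen-Nurminen). Give it for any adverse event, diarrhoea, and events of Grade 3 or higher, counting every patient who took trial drug. Keep the chi-square P value as a supplement.

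In the Discussion, replace the phrase about safety being confirmed with a statement of the largest excess risk that the interval does not exclude. Add that a P value of 0.05 or more will not be taken as evidence of safety.

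The cost is wording and a few table columns, with no extra patients, visits or data. The change adds no power, and the safety statement will be less favourable than the one now foreseen.

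### Secondary outcomes measured at baseline and 1 year are assigned unadjusted two-sample tests; ANCOVA on the baseline value would be at least as precise in large samples, at no extra cost

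*Protocol article*

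**What the plan says.** The Statistical analysis section of the protocol article gives polyp prevalence and safety to the chi-square test. It then says "The remaining results in the two groups will be compared by the Mann-Whitney" U test or Student's t test. No covariate is named, and the analysed quantity (1-year value or change) is not stated.

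Under Outcome measurements, the effect on insulin resistance and lipids is to be assessed by "comparing these parameters measured at the baseline and at 1 year in the metformin group and placebo group". The same section says "All participants will receive physical examination and laboratory tests at the time of the 1-year endoscopic examination and polypectomy". Polyps found at the repeat colonoscopy are to be biopsied, whereas polypectomy is the entry procedure, so the natural reading is two time points: entry and 1 year. For BMI the baseline value must exist in any case, because the Randomization section uses BMI as a minimisation factor.

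The ACF count is introduced with "At the time of the 1-year colonoscopy and polypectomy, the lower rectal region". A baseline count follows only if polypectomy there again means the entry procedure.

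**The concern.** When an outcome has been measured before treatment, part of its variation at 1 year is a stable difference between patients. A two-sample test on 1-year values leaves that part in the standard error. A two-sample test on change removes it by subtracting the whole baseline value, which over-corrects when the correlation is modest. ANCOVA estimates how much of the baseline value to remove.

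At stake is the precision of the metabolic, laboratory and body-weight comparisons in a trial of 150 patients. Those comparisons are meant to show what low-dose metformin does in people without diabetes. A wider interval than the data require makes a null result on them harder to interpret.

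**Working it through.** **Inputs**

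- Tests: Mann-Whitney U or Student's t, two groups, unadjusted (Statistical analysis).
- Two measurement times: baseline and 1 year (Outcome measurements).
- Patients per arm at 1 year: 68 (Sample size estimation); 75 × 0.9 = 67.5 agrees.
- Correlation r between baseline and 1-year values: not in the document. Assumed, 0.2 to 0.7.
- Equal SD at both times: assumed for the table below.

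**The plan's own figure.** The article states no power or sample size for any secondary outcome, so there is nothing to reproduce on this point. Its 68 per group is for polyp occurrence, 54.2% against 31.3%. The unpooled formula gives (0.5417 × 0.4583 + 0.3125 × 0.6875) × (1.960 + 0.842)² / 0.2292² = 69.2, within two patients of 68 after rounding up; the pooled formula gives 72. That difference has no bearing here. The 68 is used below only as the number per arm.

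**Variance per patient of each analysis** (s0 = baseline SD, s1 = 1-year SD, large samples, common slope):

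- 1-year value: s1²
- Change: s0² + s1² − 2·r·s0·s1
- ANCOVA: s1²·(1 − r²)

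The 1-year variance exceeds the ANCOVA variance by r²·s1². The change variance exceeds it by (s0 − r·s1)². Neither quantity can be negative, so ANCOVA is no less precise under either reading, whatever the SDs.

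With s0 = s1, relative to s1², the three variances are 1, 2(1 − r) and 1 − r². The saving is r² against 1-year values and 1 − (1 − r²)/[2(1 − r)] = (1 − r)/2 against change.

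| r | Change | ANCOVA | Saving vs 1-year value | Saving vs change |
|---|---|---|---|---|
| 0.2 | 1.60 | 0.96 | 4% | 40% |
| 0.3 | 1.40 | 0.91 | 9% | 35% |
| 0.5 | 1.00 | 0.75 | 25% | 25% |
| 0.7 | 0.60 | 0.51 | 49% | 15% |

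**The same in power.** Take the difference that gives 80% power on 1-year values with 68 per arm, two-sided 5%: (1.960 + 0.842) × √(2/68) = 0.48 SD.

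| r | Power, 1-year value | Power, change | Power, ANCOVA | n per arm for 80%: 1-year / change / ANCOVA |
|---|---|---|---|---|
| 0.2 | 80.0% | 60.1% | 81.6% | 68 / 109 / 66 |
| 0.3 | 80.0% | 65.8% | 83.6% | 68 / 96 / 62 |
| 0.5 | 80.0% | 80.0% | 89.9% | 68 / 68 / 51 |
| 0.7 | 80.0% | 95.1% | 97.5% | 68 / 41 / 35 |

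Low r favours the 1-year value over change, and high r does the reverse. ANCOVA is the best of the three at every r shown. These variances describe the t test. For Mann-Whitney the figures are a guide only.

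**The case against.** The strongest reply is that this is detail for an analysis plan, and a journal article is entitled to leave it there. That would hold if the article were silent. It is not: it names the tests for all remaining results, and an analysis plan using ANCOVA would depart from them. What stands is that a plan not shown may already define the analysed quantity or an adjusted model.

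The second reply is that the named tests are sound. That stands. Under randomisation an unadjusted comparison of the arms is unbiased, whether on 1-year values or on change. Only precision is lost.

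Three stronger readings are tempting, and the article does not support them:

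- **That the plan ignores baseline.** It does not say so. A two-sample test on change uses the baseline value and fits both the test named and the statement that parameters are compared "comparing these parameters measured at the baseline and at 1 year in the metformin group and placebo group".
- **That the plan tests before against after within each arm.** The same sentence can be read that way, but no paired test is named anywhere and the Statistical analysis section compares two groups.
- **That a large gain is established.** ANCOVA in place of 1-year values is worth 1/(1 − r²) in sample size: 33% more patients at r = 0.5 and 96% more at r = 0.7, but only about 4% at 0.2 and 10% at 0.3. The SDs cancel, so the ACF SDs quoted in the article lend this gain no support.

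**Conclusion.** The point holds as one of efficiency. The article commits the secondary outcomes to unadjusted two-sample tests and leaves the analysed quantity open. Whichever quantity is meant, the test is valid but, in large samples, no more precise than ANCOVA on the baseline value.

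The size is uncertain because r is not given. If 1-year values are meant, the loss is negligible at low r and substantial at high r; if change is meant, the order is reversed. The percentages assume equal SDs at the two times, but the direction does not.

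The baseline measurement is explicit for the insulin-resistance and lipid measures. For BUN and creatinine it rests on reading polypectomy as the entry procedure. For ACF it is no more than an inference. The primary endpoint and its sample size are unaffected.

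**What to change.** For each continuous secondary outcome with a baseline value (glucose, insulin, HbA1c, lipids, BUN, creatinine, weight, BMI), state that the 1-year value is compared between arms by ANCOVA with the baseline value as covariate, on a log or rank scale if the measure is skewed. Report the adjusted difference, or ratio on the log scale, with its 95% CI. Treat ACF in the same way with a count model that includes the baseline count, but only if such a count is taken; say plainly whether it is. Add one sentence saying that the between-arm comparison is the test of drug effect, which settles the ambiguous wording under Outcome measurements.

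The cost is wording. Where the baseline value is already taken, no extra patients, visits or measurements are needed.
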